### Statistical analysis

3.13

The Wilcoxon signed ranks test on the T0-T1-T2 differences concerning the different clinical outcome measures (EDSS, FIM, MAs, 10mW, 6MW, HSD, MSQOL 54) will be carried out in both groups. The α-level for significance will be set at *P* < 0.05. The Bonferroni correction will be used in multiple comparisons. Data will be expressed as mean or percentage ± standard deviation. The effects of the treatment on RMT, peak-to-peak MEP amplitude, SICI, and ICF will be evaluated in separate repeated-measures analyses of variance (rmANOVA). For each dependent variable, we will compute a 2-way rmANOVA with time (4 levels: T_0_- T_1_-T_2_) and group (2 levels: group A and group B) as within-subject factors. Conditional on a significant F value, post-hoc paired-sample *t* tests were performed to explore the strength of main effects and the patterns of interaction between experimental factors. The Greenhouse-Geisser method will be used if necessary to correct for nonsphericity. All data will be given as means or percent ± standard error. We also will calculate a Fisher Z-transformation concerning the correlations between clinical and electrophysiological parameters.

This is a pilot study. The main aim is to provide evidence which could allow planning of a further confirmatory study. The simple size of 40 patients was determined on the basis of feasibility criteria. Consequently, no formal statistical hypothesis was done

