## Objectives

2

Aim of the study is to clarify the role of Sativex coupled to a robotic neurehabilitation training in improving motor outcomes, by means of clinical, kinematic, and neurophysiological measures in patients with MS affected by spasticity.

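### The seven listed clinical measures get only within-group tests, so no planned test compares Sativex with control on the clinical motor outcomes

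*Protocol article*

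**What the plan says.** The Objectives section sets the question: "Aim of the study is to clarify the role of Sativex coupled to a robotic neurehabilitation training in improving motor outcomes", judged by clinical, kinematic and neurophysiological measures. The Trial design section describes an active-controlled, parallel-group pilot, and the Study population section gives Lokomat training to both groups.

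The Statistical analysis section then splits the outcomes in two:

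- Clinical measures: "The Wilcoxon signed ranks test on the T0-T1-T2 differences concerning the different clinical outcome measures", for "EDSS, FIM, MAs, 10mW, 6MW, HSD, MSQOL 54) will be carried out in both groups". No other test is named for these seven.
- TMS measures: "The effects of the treatment on RMT, peak-to-peak MEP amplitude, SICI, and ICF will be evaluated in separate repeated-measures analyses of variance (rmANOVA"), with time "and group (2 levels: group A and group B) as within-subject factors". If F is significant, "post-hoc paired-sample *t* tests were performed to explore the strength of main effects and the patterns of interaction between experimental factors".

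The same section adds a 0.05 significance level, a Bonferroni correction without a defined family, and a statement that this is a feasibility-sized pilot meant to inform a confirmatory study.

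**The concern.** The aim is a contrast: what Sativex adds when both groups have the same robotic training. The clinical measures, including both walking tests, are analysed by asking separately whether A changed and whether B changed. The only way to reach a statement about Sativex from that output is to compare two p-values. Two arms with the same true change can easily fall on opposite sides of 0.05. Two arms with different true changes can both fall below it.

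At stake are a Sativex benefit on walking or spasticity claimed where there is none, or a real difference missed. The planned confirmatory study would also lack the between-group estimate it needs.

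**Working it through.** **What each planned analysis can compare**

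| Outcomes | Planned analysis | A against B? |
|---|---|---|
| EDSS, FIM, MAS, 10mW, 6MW, HRSD, MSQOL-54 | Wilcoxon signed-rank in each group | No |
| RMT, MEP amplitude, SICI, ICF | rmANOVA, time and group | Intended, but mis-specified |

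In the second row each patient belongs to one group only, so group is a between-subject factor. Treating it as within-subject pairs unrelated patients. A paired comparison of A with B would have 20 − 1 = 19 degrees of freedom instead of 20 + 20 − 2 = 38, and its result would depend on the order of the records. The post-hoc paired t tests have the same fault wherever they are meant to compare groups. Time is given four levels but only T0, T1 and T2 are named.

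**How often the two within-group tests disagree when the arms do not differ**

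The plan states no figure for this, so there is none to reproduce. Inputs:

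- 20 patients per arm (Eligibility criteria) and alpha 0.05 (Statistical analysis). Two-sided testing is assumed.
- Normal change scores with the same standardized improvement d in both arms. The document gives no within-arm effect, so d is an assumption and is run from 0 to 1.0 SD.

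Let p be the chance that one arm's signed-rank test is significant. The arms are independent, so P(disagree) = 2p(1 − p) and P(A significant, B not) = p(1 − p). The exact two-sided 5% critical value at n = 20 is 52, with true size 0.0484. For d above 0, p was simulated with 200,000 samples per value.

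| d (SD) | p | 2p(1 − p) | p(1 − p) |
|---|---|---|---|
| 0 | 0.048 | 9% | 5% |
| 0.3 | 0.235 | 36% | 18% |
| 0.4 | 0.379 | 47% | 24% |
| 0.5 | 0.542 | 50% | 25% |
| 0.6 | 0.697 | 42% | 21% |
| 0.7 | 0.824 | 29% | 14% |
| 0.8 | 0.912 | 16% | 8% |
| 1.0 | 0.985 | 3% | 1% |

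Example at 0.4: 2 × 0.379 × 0.621 = 0.47. The maximum is at p = 0.5: 2 × 0.5 × 0.5 = 50%, and 25% for 'A only'. A Mann-Whitney test on the same changes rejected in 4–5% of simulated trials throughout.

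Bonferroni does not cure this; it moves the peak to a larger d. With an assumed family of three (alpha 0.05/3), p at d = 0.4 is 0.22, so disagreement is 2 × 0.22 × 0.78 = 34%.

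**The reverse error**

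Suppose the arms truly differ: 1.20 SD improvement in A and 0.59 SD in B (assumed, 0.61 SD apart). Then p is 0.999 in A and 0.683 in B. Both are significant in 0.999 × 0.683 = 68% of trials, which would read as no difference.

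**The case against.** - **A comparison is planned.** A reader might infer that nothing in the plan compares Sativex with control and that the trial cannot answer its question. That goes too far. A time-by-group rmANOVA is planned for the TMS measures, and neurophysiology is part of the stated aim. The gap concerns the clinical measures. The Sample size section speaks of an interaction in a two-way repeated-measures design with seven variables, which may hint at a comparison for the clinical scales. The Statistical analysis section does not assign them one.
- **Not every clinical outcome is affected.** NRS is among the Outcome measures but not in the Wilcoxon list. It has no named test in the article, which is different from a wrong one.
- **It is a pilot with no formal hypothesis.** This limits the consequence, since no confirmatory claim rests on these tests. It does not turn two within-group tests into a comparison.
- **The error rates depend on the assumed effect.** This stands. The Background calls the evidence on robotic training in MS conflicting, so improvement in both arms cannot be taken for granted. Disagreement is small near 0 and from about 1.0 SD upwards.
- **SD and SE.** The section promises SD in one place and, later, "All data will be given as means or percent ± standard error". A reader might infer that an SE will be taken for an SD and the next trial mis-sized. The SD statement follows the clinical tests, the SE statement follows the TMS analyses, and each is labelled. The wording is untidy, but the document does not support that inference.
- **An unseen analysis plan might add the comparison.** The article does not leave the choice open. It names the test, and the named test is of the wrong kind.

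**Conclusion.** Wrong as written for the seven listed clinical measures. The stated test cannot compare the arms, while the objective is comparative. This follows from the text and needs no assumption.

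The size of the inferential risk does rest on assumptions: normal changes, equal standardized improvement in both arms and 20 patients per arm. Under these, 'A significant, B not' arises with no Sativex effect in at most about 25% of trials. It falls to about 8% at 0.8 SD and 1% at 1.0 SD. For the TMS measures a comparison is planned, but with group in the wrong stratum.

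A correct between-group test would still not give the randomized effect of Sativex. By the Eligibility criteria and Prescreening sections, Group A is limited to patients who responded to a month of Sativex, while Group B simply continued its treatment. The Abstract calls the Group B patients non-responders, which makes the groups no more comparable.

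**What to change.** 1. For each clinical outcome, estimate the A−B difference at T1 and at T2. Use ANCOVA with the T0 value as covariate, or a mixed model with group as a between-subject factor and a group-by-time term. For ordinal scales such as EDSS and MAS, use a rank-based between-group test of the change.
2. Report each difference with its 95% CI and the group SDs. Keep the within-group Wilcoxon tests as description only, and state that no treatment effect will be inferred from them.
3. In the TMS rmANOVA, declare group between-subject, reconcile the number of time levels with the visits, and use unpaired contrasts where groups are compared.
4. State that the A−B difference does not estimate the randomized effect of Sativex, because Group A is restricted to responders. If T0 falls after the month of trial treatment, the adjusted difference also leaves out any gain already made by then.

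The protocol ranks no outcome, so the choice of a lead comparison stays with the investigators.

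The cost is wording; no new data or visits are needed. Against an analysis of change scores, ANCOVA multiplies the variance by (1 − r²)/(2(1 − r)) = (1 + r)/2, where r is the correlation with baseline: 0.75, 0.85 and 0.90 for assumed r of 0.5, 0.7 and 0.8. Intervals will still be wide. With 20 per group the half-width is about 2.02 × √(2/20) = 0.64 SD of the analysed quantity, which is what a pilot of this size can honestly report.

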### Trial design

3.1

This is a rater-blinded, active-controlled, parallel-group pilot study to assess the efficacy of Sativex associated with robotic-rehabilitation in improving the motor performances of Multiple Sclerosis patients. This study will be conducted at the IRCCS Centro Neurolesi Bonino-Pulejo in Messina, Italy. The study protocol was approved by the Ethical and Research Committee of IRCCS Centro Neurolesi Bonino-Pulejo (13/2016 vers, n 1 23/11/2016). The trial is registered under trial gov. (NCT03186664). The study purpose will be explained to the participants, and patients’ consent will be obtained before the enrollment by the principle investigator.

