### Outcome measures

3.10

Patients will be clinically evaluated by means of an accurate neurological examination by a blind to treatment physician through validated scales: EDSS, Functional Independence Measure (FIM), MAS, NRS, 10mW, 6 minute walking test (6MW), Hamilton rating scale for Depression (HRSD), and MSQOL 54. Muscular stiffness and strength will be also evaluated by means of instrumental measures furnished by the neurorobotic device itself. Moreover, cortical plasticity will be evaluated by means of TMS methodology. Finally, blood pressure and mean heart rate will be assessed.

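### No outcome, visit or between-group contrast is named to answer the efficacy question, and the Bonferroni rule names no family, so the error rate of the 28 to 42 within-group clinical tests is undetermined

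*Protocol article*

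**What the plan says.** Section 3.1 (Trial design) calls the trial a "pilot study to assess the efficacy of Sativex associated with robotic-rehabilitation in improving the motor performances". Section 2 (Objectives) speaks of motor outcomes judged by clinical, kinematic and neurophysiological measures. Section 3.10 (Outcome measures) has patients assessed "through validated scales: EDSS, Functional Independence Measure (FIM), MAS, NRS, 10mW, 6 minute walking test (6MW"), followed by a depression scale and MSQOL-54, then device-measured stiffness and strength, then TMS. Sections 3.6 and 3.11 give similar lists. None of them ranks the outcomes, and none says which visit or comparison counts most.

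Section 3.13 (Statistical analysis) fixes the tests:

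- For the clinical scales the plan names "The Wilcoxon signed ranks test on the T0-T1-T2 differences concerning the different clinical outcome measures (EDSS, FIM, MAs, 10mW, 6MW, HSD, MSQOL 54"). These tests are run separately within Group A and within Group B.
- The significance level is 0.05. On multiplicity, the only rule is this: "The Bonferroni correction will be used in multiple comparisons".
- Four TMS measures "will be evaluated in separate repeated-measures analyses of variance (rmANOVA"), with time and group as factors. Post-hoc t tests follow a significant F.
- Correlations between clinical and electrophysiological measures are added.

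The section closes by saying that this is a pilot meant to inform a confirmatory study, that 40 patients were chosen for feasibility, and: "Consequently, no formal statistical hypothesis was done". Section 3.12 (Sample size), by contrast, gives a power above 80% for an interaction, without saying on which outcome.

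**The concern.** A trial that sets out to assess efficacy needs one stated comparison that answers the question. Here the candidates measure different things: walking speed, endurance, tone, function, depression, quality of life and cortical excitability. They may disagree, and nothing in the text prevents the emphasis from being chosen after the data are seen. Because the pilot is meant to shape a confirmatory study, that choice could carry straight into the next trial's endpoint.

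There are two further weaknesses. The clinical analysis as written looks only at change inside each group, which does not address what Sativex adds. And the one sentence on multiplicity cannot be applied without deciding what it covers. Two analysts following it faithfully could declare the same result significant and not significant.

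**Working it through.** **Plan's own figure.** The document states no family-wise error rate, so there is none to reproduce. Its only design figure is 36 per group at effect size 0.61 (section 3.12). Read as a two-group standardised difference, n = 2(1.960 + 0.842)²/0.61² = 42.2, so 43 per group two-sided. One-sided it is 2(1.645 + 0.842)²/0.61² = 33.2, so 34. Neither is the interaction test described, and the effect metric and within-patient correlation are not given. Nothing below depends on this figure.

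**Step 1: count the tests (section 3.13).** There are seven clinical outcomes, two groups and three visits.

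- Changes from baseline only: 7 × 2 × 2 = 28 tests.
- All pairs of visits: 7 × 3 × 2 = 42 tests.
- TMS: 4 interaction tests, or 4 × 3 = 12 F tests with both main effects, plus conditional post-hoc tests and the correlations.

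**Step 2: what the clinical tests compare.** The signed-rank test is paired and is run in each group separately. Section 3.6 gives Lokomat training to both groups. A significant change in Group A may therefore be Sativex, training, time or any mixture. The only between-group comparison planned anywhere is through the group factor in the four TMS analyses.

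**Step 3: thresholds that fit the Bonferroni sentence.**

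| Family | Divisor | Per-test level |
|---|---|---|
| Visit pairs within an outcome | 3 | 0.0167 |
| Outcomes | 7 | 0.0071 |
| All tests in one group | 21 | 0.0024 |
| All clinical tests | 42 | 0.0012 |

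P = 0.01 is significant under the first reading and under none of the others.

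**Step 4: chance of at least one significant result among the 42 tests when nothing changes.** The inputs are two-sided 0.05 (sidedness assumed), two independent groups, and visit contrasts that share visits. The correlation r between outcomes is not in the document and is assumed to lie between 0 and 0.9. Results from simulated correlated z-scores:

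| Divisor | r = 0 | r = 0.5 | r = 0.9 |
|---|---|---|---|
| 3 | 46.8% | 37.5% | 20.0% |
| 7 | 24.2% | 19.8% | 10.0% |
| 21 | 9.0% | 7.8% | 3.9% |
| 42 | 4.6% | 4.1% | 2.2% |
| none | 84.0% | 72.5% | 44.7% |

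The last row is for reference only, since the plan promises a correction. A simulation of the signed-rank test itself with 20 per group gives somewhat lower values. With divisor 3 it gives 41%, 35% and 26% at r = 0, 0.5 and 0.8. With divisor 42 it gives 1.3%, 1.7% and 1.6%. The picture is the same.

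**Step 5: TMS.** Whether Bonferroni reaches across the four analyses is not said. If it does not, and treating them as independent, the four interactions alone give 1 − 0.95⁴ = 18.5%.

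**Step 6: power of one between-group contrast.** With 20 per group and an assumed standardised difference of 0.61, the noncentrality is 0.61 × √(20/2) = 1.93 on 38 degrees of freedom. A two-sided 0.05 t test then has power of about 47%. The 0.61 is borrowed from section 3.12, where it describes something else, so this figure is only indicative.

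**The case against.** The strongest reply is that this is a pilot. Section 3.13 says so, gives feasibility as the basis for 40 patients and disclaims a formal hypothesis. Family-wise control over every outcome is not normally asked of such a study. That stands, and it lowers the stakes. It does not remove the conflict. The same section sets a significance level, promises Bonferroni and opens post-hoc tests on a significant F; section 3.1 speaks of efficacy; section 3.12 claims power. Nowhere are the tests called exploratory.

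A second reply is that a journal article leaves the Bonferroni divisor to a fuller document. Taken alone, the divisor would be a small matter. But the article does state the rule, in a form that several incompatible families satisfy, and it also fixes a clinical analysis with no between-group test.

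A reader might infer that the trial's false-positive rate is known to be some 35% to 74%. The documents do not support that. The upper figure assumes no correction, which section 3.13 rules out. The lower is one reading (divisor 3) at one assumed correlation (0.5), and stricter readings that comply equally well hold the rate near or below 5%.

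A reader might also infer that every chance rejection among the 42 tests is a false efficacy finding. That does not follow either: a within-group change is not evidence about Sativex whether it is real or not.

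**Conclusion.** The point holds in a limited form. No outcome, visit or contrast is designated to answer the efficacy question. The 28 to 42 clinical tests are unranked and within group, so they cannot isolate a Sativex effect. The Bonferroni family is undefined. The family-wise rate for the 42 clinical tests is therefore undetermined: about 2% to 5% with divisor 42, rising to about 20% to 47% with divisor 3. These ranges rest on an assumed correlation between outcomes of 0 to 0.9 and on two-sided testing. The defect is the ambiguity and the missing comparison, not a demonstrated high error rate.

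It might also be inferred that naming one contrast would turn this into a valid 5% confirmatory test. It would not. Section 3.4 (Prescreening) fills Group A with the first 20 responders to Sativex, and Group B with patients who continued their treatment and were not selected in that way. The comparison stays a selected one whatever is named.

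**What to change.** In section 3.13:

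1. Name one main between-group contrast. An example is Group A versus Group B on the change in the 10 m walk from T0 to T1; it is the only walking test in every outcome list (sections 3.6, 3.10, 3.11 and 3.13). The final choice is the sponsor's.
2. Report it as an estimate with a 95% confidence interval, labelled a pilot result because Group A is selected on response.
3. Label all other clinical outcomes, T2, the TMS analyses and the correlations exploratory, with no efficacy claim.
4. State the Bonferroni family, for example the time comparisons within each outcome, and say that it does not control error across outcomes.
5. Make the group-by-time interaction the F test that supports a treatment effect on the TMS measures.

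The cost is a few sentences, with no new data or patients. The sponsor commits to one outcome and gives up efficacy claims from the others. The modest power in step 6 is a further reason to rest on the interval and not on a P value.

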### Eligibility criteria

3.2

We will enroll 40 MS patients affected by gait disturbances and moderate-severe spasticity: 20 of them in treatment with Sativex (Group A) considered as responders, and 20 treated only with the most common antispastics used in MS (Group B). Inclusion criteria are: age range 18 to 65 years; diagnosis of definite relapsing-remitting or primary-progressive or secondary-progressive multiple sclerosis; absence of clinical relapses from no gadolinium-enhanced lesions on brain and spinal cord MRI performed at least 6 months before study entry; no mood or sleep disorders with an Hamilton score of ≤17; a moderate to severe spasticity in at least 2 districts of upper and/or lower limbs; absence of clinical or neuroradiological relapses from at least 6 months before study entry; Expanded Disability Status Scale (EDSS) total score between 3.5 and 7.0; no history of psychosis; no presence of pace-maker, aneurysms clips, neurostimulator or brain/subdural electrodes (safety TMS procedure); right handedness, central conduction time in upper limbs of <8 ms; no robotic gait training contraindications.

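### The Bonferroni correction named in the plan is valid, but Holm's step-down procedure keeps the same error bound and can add power once a first comparison is rejected

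*Protocol article*

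**What the plan says.** Section 3.13 (Statistical analysis) of the protocol article plans Wilcoxon signed-rank tests of the changes between visits, separately within each group, for seven measures: "clinical outcome measures (EDSS, FIM, MAs, 10mW, 6MW, HSD, MSQOL 54) will be carried out in both groups". The significance level is 0.05, and the correction is then named: "The Bonferroni correction will be used in multiple comparisons". The text does not say which comparisons form a family, whether the tests are two-sided, or whether a single-step or step-down form is meant. Without qualification, the name ordinarily means the single-step rule, in which each of m tests is held at 0.05/m.

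Section 3.2 (Eligibility criteria) gives the group sizes: "20 of them in treatment with Sativex (Group A) considered as responders, and 20 treated only with the most common antispastics". Section 3.13 also calls the trial a pilot: "The main aim is to provide evidence which could allow planning of a further confirmatory study".

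**The concern.** The single-step rule keeps every comparison at 0.05/m, even after other comparisons in the family have been rejected. Holm's procedure relaxes the threshold after each rejection without loosening the family-wise bound. Several of the listed outcomes (walking tests, functional independence, spasticity) may well change together under gait training, although the article does not say so. With 20 patients per group, that is the setting in which the stricter thresholds cost most.

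At stake is how many truly changed outcomes are recognised. That has some value in a pilot meant to inform a later trial. No stated result or sample size depends on it.

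**Working it through.** **Figure to reproduce.** The article gives no number for the Bonferroni step, so there is none.

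**Inputs.**
- Family-wise level 0.05 (section 3.13). Two-sided is my assumption.
- n = 20 per group (section 3.2).
- Wilcoxon signed-rank tests within a group (section 3.13).
- m = 7, if the family is the seven listed clinical outcomes (assumption).
- True change of 0.61 SD. Section 3.12 (Sample size) gives 0.61 as the document's only effect size but does not state its type. I read it as a standardised within-patient change (assumption).
- Correlation between outcomes 0.3 or 0.6 (assumption).

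**Thresholds for m = 7.** Bonferroni uses 0.05/7 = 0.0071 for all seven. Holm orders the P values and tests the j-th smallest at 0.05/(7 − j + 1), stopping at the first failure:

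| j | 1 | 2 | 3 | 4 | 5 | 6 | 7 |
|---|---|---|---|---|---|---|---|
| Holm | 0.0071 | 0.0083 | 0.0100 | 0.0125 | 0.0167 | 0.0250 | 0.0500 |

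No Holm threshold is below 0.0071, so Holm rejects whatever Bonferroni rejects. The first threshold is the same, so the two methods reject at least one hypothesis in exactly the same data sets.

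**Error bound.** Suppose m0 null hypotheses are true. When Holm first rejects a true one, at least m0 hypotheses remain, so the threshold is at most 0.05/m0. The probability that the smallest of m0 true-null P values falls below this is at most m0 × 0.05/m0 = 0.05, whatever the correlation.

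**Size of the gain.** Simulation of the exact Wilcoxon signed-rank test, n = 20, m = 7, changes of 0.61 SD; mean power per truly changed outcome:

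| Outcomes truly changed | Bonferroni | Holm | Gain (points) |
|---|---|---|---|
| 1 | about 38% | about 38% | about 0 |
| 2 | about 38% | about 40% | about 2 |
| 4 | 38% | 42–43% | 4–5 |
| 7 | 38–39% | 49–50% | about 11 |

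If all seven change by 0.7 SD, power goes from 52–53% to 66–67%, a gain of 13–14 points. Holm missed no Bonferroni rejection. Family-wise error was about 4% or below for both methods, and identical when no outcome changes.

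**A smaller family.** If the correction applies to the three time contrasts of one outcome, Bonferroni uses 0.05/3 = 0.0167. With both changes from T0 at 0.61 SD, no T1–T2 change and correlation 0.5 between visits, power per true contrast goes from about 52% to about 56%, a gain of 4 points.

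**Realised error.** Using paired t tests in place of Wilcoxon, with four of seven outcomes changed, the family-wise error among the other three is about 2.0–2.1% with Bonferroni and 3.0–3.1% with Holm. Holm uses more of the allowance but stays inside it.

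**The case against.** The strongest reply is that nothing here is wrong. Bonferroni is valid, prespecified and conservative, and nothing in the article contradicts it. The trial is a feasibility-sized pilot for which "Consequently, no formal statistical hypothesis was done". This stands, and it is why the point is an improvement and not a correction. It does not remove the point: the same section sets an alpha level and a multiplicity adjustment, and once family-wise control is chosen there is little reason to take the less powerful of two procedures with the same guarantee.

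A second reply is that Bonferroni has advantages of its own: one fixed threshold and simple matching simultaneous confidence intervals. This is true, but section 3.13 reports means or percentages with SD or SE and mentions no such intervals.

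A third is that these clinical tests are within group and both groups train on the robot, so more within-group rejections would not isolate the role of Sativex. This also stands and limits the consequence.

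A reader might also infer more than the documents support:
- *Every outcome loses power.* Holm gains nothing until another comparison has been rejected, and almost nothing if only one outcome changes.
- *The plan fixes each test at 0.0071.* The family of seven is an assumption. The sentence could equally concern the three time contrasts.
- *The gain extends to between-group rank tests of the clinical outcomes.* Section 3.13 contains no such test.

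**Conclusion.** The point holds as a low-severity matter of efficiency. For testing, Bonferroni is uniformly dominated by Holm, which has the same family-wise bound of 0.05, requires no added assumption and never loses a rejection. At 0.61 SD and n = 20 the gain in mean power per truly changed outcome runs from practically nil to about 11 points for a family of seven, and is about 4 points for three time contrasts with two real changes. The direction does not depend on the assumptions. The size depends on the family, the number of true changes and their magnitude, none of which the article settles. The chance of at least one rejection does not change. It would be wrong to report this as an error in the plan or as something that invalidates a planned conclusion.

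**What to change.** Replace the Bonferroni sentence in section 3.13 with: *Within each family of comparisons, P values will be adjusted by the Holm step-down procedure (two-sided family-wise 0.05).* Report the Holm-adjusted P values beside the unadjusted estimates. If a step-down form was already intended, the same sentence makes that clear.

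The cost is one sentence and one software option, with no extra patients or data. Simultaneous confidence intervals that match Holm are less simple than Bonferroni intervals. If the sponsor wants such intervals, keeping Bonferroni for them is defensible.
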